## Methods and analysis

### Design

A two-arm (online CBT vs waiting list) multicentre open label parallel randomised controlled trial (RCT) will be conducted. Randomisation will take place after the participant is screened for eligibility-based inclusion criteria (described below). A random number generator (www.random.org) will be used by a blinded independent researcher, to perform the blocking randomisation procedure. An allocation ratio of 1:1 will be applied.

Participants allocated to the online CBT condition receive treatment within 1 week after allocation. All participants will be asked to fill in questionnaires (described below) at baseline (T1), 12 weeks postallocation (T2 for the intervention condition and T1a for waitlist controls) and 20 weeks postallocation (T3 for the intervention condition and T1b for waitlist controls). For participants in the waiting list control group, at the end of the 20-week waiting period after which they will receive online CBT, they will be asked to fill in T2 and T3 12 and 20 weeks after starting treatment, respectively (see figure 1). A link to online questionnaires will be sent to the participants by a non-blinded member of the research team at each time point. A waitlist control group (instead of a no treatment control group) is chosen to increase the likelihood of continued study participation by guaranteeing that all participants receive treatment. Furthermore, the inclusion of a waiting list control group allows a treatment versus no treatment comparison that will provide knowledge about the effects of treatment relative to natural recovery from loss.

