#### Other measures

Background characteristics (ie, gender, age and educational level, kinship to the deceased and time since loss) and accident-related stressors (ie, single vs multiple loss, witnessed the accident and status of legal trial) will be assessed with single items.

Participants are allowed to receive other forms of psychosocial, instrumental or legal support during participation in the trial. Using a single question, we will assess whether the participants received other forms of psychosocial professional support. The following question will be used: ‘During the past 12 weeks/8 weeks (for T2 and T3, respectively) did you receive additional psychological professional support from a psychologist, therapist or psychiatrist other than the (online) therapist from the TrafVic-study?’ We will also include two dichotomous items (yes/no) at T1 to assess psychological support received prior to participation in the study, namely: ‘Did you ever receive support from a psychologist, therapist or psychiatrist, for your own emotional/mental problems, prior to the loss of your loved one due to a traffic accident?’ and ‘Did you ever receive support from a psychologist, therapist or psychiatrist, for your own emotional/mental problems, related to the loss of your loved one due to a traffic accident?’

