### Statistical analyses

To examine the differences in reductions of symptom levels of PCBD, PTSD and depression from pretreatment to post-treatment/waiting period between the conditions (online CBT vs waitlist), three independent multilevel models will be built (hypothesis 1). Symptom levels of PCBD, PTSD, and depression will consecutively be included as dependent variables and condition (online CBT vs waitlist controls), time and time × condition (interaction term) as predictor variables, taking into account that repeated observations (level 1) are nested within individuals (level 2), and within households (level 3; if applicable). Additionally, relevant background, loss-related variables and use of cointerventions (yes/no) during participation in our study will be included in the analysis as covariates. Deviance tests will be used to examine whether inclusion of these covariates improves model fit.^57^ Data of all participants entering the study will be included in all analyses (ie, intention-to-treat analysis). Furthermore, percentages of people meeting diagnostic criteria for PCBD, PTSD and clinically relevant depression will be calculated for each measurement occasion and percentages of people reporting reliable change scores for each outcome measure, using a formula from Jacobson and Truax,^58^
^p 14^ will be reported.

To examine to what extent symptom improvement after treatment is related to improvement in possible correlates of change, residual gain scores will be calculated for all outcome measures (ie, PCBD, PTSD and depression) and possible correlates of change (ie, negative cognitions, avoidance behaviours, state anger, a sense of unrealness and self-efficacy). Following previous research^59^, residual gain scores will be calculated by subtracting the standardised combined pretreatment scores of both conditions (T1 data from immediate treatment condition and T1b data from waitlist condition) multiplied by the correlation coefficient between standardised combined pretreatment scores and standardised post-treatment (or follow-up) scores from standardised post-treatment (or follow-up) scores. To test hypothesis 2a, multiple regression analyses will be conducted to examine the associations between residual gain scores of PCBD, PTSD or depression and residual gain scores of negative cognitions, avoidance behaviours, state anger, a sense of unrealness and self-efficacy.

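### Co-intervention use, measured after randomisation, is a covariate in the primary models and, depending on how it enters, may move the time × condition estimate away from the effect of allocation

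*Protocol article*

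**What the plan says.** Statistical analyses section: each of the three hypothesis 1 models has "condition (online CBT vs waitlist controls), time and time × condition (interaction term) as predictor variables". Background variables and loss-related variables are added as covariates, and so is a third kind: "use of cointerventions (yes/no) during participation in our study will be included in the analysis as covariates". The next sentence says: "Deviance tests will be used to examine whether inclusion of these covariates improves model fit". The same paragraph states: "Data of all participants entering the study will be included in all analyses (ie, intention-to-treat analysis". No model without co-intervention use is named as primary.

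Other measures section: "Participants are allowed to receive other forms of psychosocial, instrumental or legal support during participation in the trial". The item that records it reads: "During the past 12 weeks/8 weeks (for T2 and T3, respectively) did you receive additional psychological professional support". It asks about support from someone other than the trial's own (online) therapist.

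Design section: the follow-up visits are "12 weeks postallocation (T2 for the intervention condition and T1a for waitlist controls"), and 20 weeks after allocation T3 and T1b respectively. Waitlist controls reach visits labelled T2 and T3 only after the wait, when "they will be asked to fill in T2 and T3 12 and 20 weeks after starting treatment, respectively". The trial is open label, and its stated comparison is treatment against no treatment.

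**The concern.** Randomisation protects a comparison adjusted for baseline variables. It does not protect one adjusted for something that happens afterwards and that allocation may influence. People who know that they must wait 20 weeks may look for other help more often than people already in therapy, and people whose symptoms run a worse course may look for it more often in either arm. Adjusting can then do two things. If the other help works, adjustment removes its benefit from the waitlist arm, and CBT looks better than allocation to CBT actually made it. If use mainly marks a worse course, adjustment makes the arms differ in prognosis at a given level of use, and CBT looks worse.

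The deviance test gives limited protection. It favours keeping the covariate when it is strongly related to the outcome, which is when adjustment can matter most.

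A second question is over which period the covariate is measured in controls, because the item is tied to T2 and T3 while the randomised comparison in that arm runs through T1a and T1b.

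**Working it through.** **1. The plan's own figure.** The sample size uses f = 0.25, r = 0.50, α = 0.017, two groups and two assessments. For the repeated-measures interaction, λ = f²·N·m/(1 − r) = 0.0625 × 46 × 2 / 0.5 = 11.5, with 1 and 44 degrees of freedom. Power is 0.814, so 23 per condition is reproduced. The calculation mentions no covariate, so dropping one does not alter it.

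**2. Which coefficient matters.** Hypothesis 1 concerns differences in reduction, so the effect is time × condition. The article does not say whether co-intervention use is one yes/no per person, a time-varying value, or a term that interacts with time. All three were examined.

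**3. Assumptions.** The article gives no usage rates, so these inputs are illustrative: outcome SD 1; pre–post correlation about 0.5; direct CBT effect δ = −0.5 SD; use on waitlist versus CBT of 30% v 10% or 50% v 10%. Two mechanisms were tried. In (a), other help lowers symptoms by g = 0.3 SD and use is unrelated to course. In (b), other help has no effect, but the log-odds of use rise by 1.0 per SD of an unmeasured worse course, which itself adds 0.4 SD to the outcome. Under (b), average use becomes 33% v 13% or 50% v 13%.

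**4. Mechanism (a) by hand**, with change regressed on arm and use.
- Effect of allocation = δ − g·(p_CBT − p_WL).
- Effect adjusted for use = δ.
- Shift = g·(p_CBT − p_WL).
- 50% v 10%: effect of allocation −0.5 + 0.3 × 0.4 = −0.38; adjusted −0.50; shift −0.12.
- 30% v 10%: effect of allocation −0.5 + 0.3 × 0.2 = −0.44; adjusted −0.50; shift −0.06.

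The shift does not depend on δ.

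**5. Simulation, change adjusted for use** (400,000 persons).

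| Use, WL v CBT | Mechanism | Without | With | Shift |
|---|---|---|---|---|
| 30% v 30% | (a) | −0.499 | −0.500 | 0.00 |
| 30% v 10% | (a) | −0.439 | −0.499 | −0.06 |
| 33% v 13% | (b) | −0.499 | −0.432 | +0.07 |
| 50% v 10% | (a) | −0.379 | −0.498 | −0.12 |
| 50% v 13% | (b) | −0.502 | −0.376 | +0.13 |
| 50% v 13% | (a) and (b) together | −0.390 | −0.376 | +0.01 |

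**6. Random-intercept models, two visits** (8,000 persons, 50% v 10–13%).

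| Form of covariate | (a) | (b) |
|---|---|---|
| None | −0.389 | −0.484 |
| Person-level main effect | −0.389 | −0.484 |
| Person-level × time | −0.514 | −0.355 |
| Time-varying | −0.508 | −0.350 |

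The main effect changes nothing, because a value that is constant within a person cannot explain change within that person. With 19% random dropout the estimates without and with the main effect still agree (−0.420 and −0.420; −0.486 and −0.486).

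**7. Three visits**, same assumed use. The person-level main effect again gives no shift. A time-varying covariate moves the estimate from −0.41 to −0.54 under (a), and from −0.47 to −0.35 under (b), that is by 0.13 and 0.12. Another set of runs under (b) gave −0.48 to between −0.39 and −0.37, a shift of 0.09 to 0.11. With covariate × time under (b), the estimate goes from about −0.48 to between −0.27 and −0.25, a shift of 0.21 to 0.23. A separate run gave −0.47 to −0.23, the same size within rounding and simulation error.

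**8. Timing of the item.** The recall windows add to 12 + 8 = 20 weeks, the length of the randomised period. In the CBT arm T2 and T3 fall at weeks 12 and 20 after allocation, so they cover it. In the waitlist arm, read literally, T2 and T3 fall 12 and 20 weeks after the start of treatment, which itself follows the 20-week wait.

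**The case against.** The strongest defence is that the plainest reading of a yes/no for use during participation is one value per person, entered as a main effect, and that form leaves time × condition untouched. This stands. A reader might infer that the CBT effect is biased as planned. The document does not support that, because it specifies neither a time-varying covariate nor an interaction with time. It does not rule them out either, and separate 12-week and 8-week questions lend themselves to a time-varying variable.

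Second, higher use on the waitlist is an inference. The article gives no rates by arm, and with equal use the shift is zero. This also stands, so only a conditional statement is possible.

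Third, a reader might infer that the covariate breaks the intention-to-treat analysis. The article uses that term for including data of all participants, which the covariate does not change. The narrower point holds: an adjusted coefficient need not equal the effect of allocation.

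Fourth, the T2/T3 wording may be condensed. The Design section says that all participants complete questionnaires at baseline, 12 and 20 weeks, and the recall windows fit T1a and T1b. It is therefore not established that controls are asked about the wrong period, only that the two sections conflict as written.

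Fifth, the article says that deviance tests examine fit; a retention rule is inferred. The exact covariate list and model-building rules commonly belong to an analysis plan, which is not shown, so their absence is not held against the article.

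**Conclusion.** The point holds in conditional form. A post-randomisation variable is placed in the primary models, and nothing limits it to the form in which it is harmless. If it is time-varying or interacts with time, and use differs by arm, time × condition may depart from the effect of allocation by about 0.06 SD at 30% v 10% use, and by about 0.12 to 0.23 SD at 50% v 10–13%. Those sizes rest on assumed rates and mechanisms and are not bounds. The direction cannot be known in advance, and when both mechanisms act together they can nearly cancel. As a person-level main effect the covariate neither harms nor helps the tested contrast. Under no form examined does it improve the estimate of the effect of allocation, so there is little reason to keep it in the primary model.

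**What to change.** - Remove co-intervention use from the primary hypothesis 1 models and adjust there only for baseline covariates.
- Use the co-intervention-adjusted model only as a sensitivity analysis, and state whether the covariate is person-level, time-varying or interacts with time.
- Report co-intervention use by arm over the randomised 20 weeks.
- Reconcile the Other measures section with the Design section, so that the item is clearly asked of waitlist controls at T1a (past 12 weeks) and T1b (past 8 weeks), in wording that fits people who do not yet have a trial therapist.

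Cost: a change of wording and, if not already planned, one item at T1a and T1b. The evaluable sample of 46 and the total of 55 stay as they are.

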**Trial registration number:**

NL7497.

Strengths and limitations of this studyThis study is the first to examine the effectiveness of online cognitive–behavioural therapy (CBT) (vs waitlist controls) in reducing psychopathology after traumatic loss in a randomised controlled trial.This study is one of the first to examine potential correlates of change in symptom levels following online treatment after traumatic loss.We are not able to formally test mediators or moderators of treatment effects.We are not able to examine if online CBT has equal effects as face-to-face CBT.We are not able to establish formal diagnoses, as we use self-report questionnaires, instead of diagnostic interviews, to assess symptom levels.

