### Sample size

To test our primary hypothesis (hypothesis 1), a test for each outcome separately (PCBD, PTSD and depression) will be conducted to assess the effects of online CBT versus waitlist controls. To find a difference between two groups (online CBT vs waitlist controls) of at least a medium effect size (f=0.25; based on prior research^22 28 40^) with a power of 80%, an α of 0.017 (corrected for multiple testing, that is, 0.05/3, as there are three primary outcome measures (PCBD, PTSD and depression), and a strong association (r=0.50) between the preassessment and postassessment, a sample size of 23 per condition is sufficient. Taking into account an average dropout rate of 19%,^22^ a total sample size of 55 (46+9) is required to test hypothesis 1.

Because our data are nested (repeated measures) (level 1) within individuals (level 2), and possibly within families sharing the same household (level 3), multi-evel modelling will be performed to test hypothesis 1. Conducting a power analysis within a multilevel framework is not feasible for various reasons.^42^ Our power analysis is therefore based on a repeated measures analysis of variance.

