To achieve research aim 2b, multiple regression analyses will be used to examine to what extent residual gain scores of PCBD, PTSD and depression varies as function of a) background characteristics, including gender (male/female), age (in years) and educational level (low/high), kinship to the deceased (child/spouse vs other) and time since loss (in years) and b) accident-related stressors, including number of losses (single vs multiple), witnessing the accident (yes/no) and status of legal trial (not applicable/ongoing/completed). Condition (intervention vs waitlist controls) will be added as a covariate to fulfil research aims 2a and 2b.

To achieve the third research aim: (1) differences in therapeutic alliance scores will be assessed between people who completed and dropped out of treatment and (2) multiple regression analyses will be used to examine to what extent symptom improvement in PCBD, PTSD and depression is related to therapeutic alliance (from both participant and therapist perspectives).

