## Discussion

The relatively few RCTs among general bereaved people with elevated grief levels indicate that grief-specific CBT-based interventions yield the largest effects on postloss mental health compared with a waiting list.^21–24^ RCTs evaluating face-to-face or online treatment effects for people with elevated mental health complaints after confrontation with sudden/violent losses are lacking, with the exception of two studies that compared face-to-face EMDR plus CBT against waitlist controls.^40 59^ Given that traumatically bereaved people are at risk for PCBD and comorbid PTSD and depression,^8^ it seems particularly relevant to develop evidence-based interventions for this population.

This will be the first RCT to examine the effectiveness of online CBT in a sample exclusively comprised of people who experienced a traumatic death. We are not able to test whether the online CBT has equal effects as face-to-face CBT. Nonetheless, the findings are expected to yield important insights in the effects of online CBT. In this RCT, the online treatment is designed to be as similar as possible to face-face CBT in terms of treatment content, treatment duration, and experience and training of therapists. When we find effect sizes for online CBT that are similar to effect sizes found in earlier studies for face-to-face CBT, delivering CBT online can be considered as supplement to face-to-face treatment, in particular when barriers to face-to-face treatments, such as waiting lists and travel expenses, are experienced.

We will also examine potential correlates of change. These analyses, examining the associations between reductions in symptoms levels and among others negative cognitions and avoidance behaviours, will provide insights in potential underlying therapeutic processes to foster recovery from traumatic loss. These insights are deemed important to design treatments that more effectively target these correlates of change. We also expect to improve our knowledge on for whom (eg, women or people who are more remotely bereaved) grief-specific CBT works best. Findings on these potential correlates of change are necessary to improve treatments given that a maximum of 42% of bereaved people report clinically relevant reductions in grief levels after treatment.^21^

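### Aim 2b regresses a baseline-residualised score on predictors not adjusted for baseline, in treated phases only, so coefficients can be biased and show predictors of outcome under treatment rather than who benefits more from CBT

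*Protocol article*

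**What the plan says.** Under Statistical analyses, the outcome for aim 2 is built in a separate first step: "residual gain scores will be calculated by subtracting the standardised combined pretreatment scores of both conditions", multiplied by the pre-post correlation, from the standardised post-treatment or follow-up scores. Pretreatment means T1 in the immediate arm and T1b in the waitlist arm, that is, the end of the 20-week wait.

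For aim 2b, "multiple regression analyses will be used to examine to what extent residual gain scores of PCBD, PTSD and depression varies as function of" five background characteristics (gender, age, education, kinship, time since loss) and three accident-related stressors (number of losses, witnessing, legal status). Condition is added as a covariate. Neither the pretreatment score nor a predictor-by-condition term is listed.

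Three places describe what this is meant to show:
- Study objectives frames 2b as relations with treatment effects and expects the stressors to affect these negatively. It describes the second aim as exploratory.
- The Discussion states: "We also expect to improve our knowledge on for whom (eg, women or people who are more remotely bereaved) grief-specific CBT works best".
- The list of strengths and limitations states: "We are not able to formally test mediators or moderators of treatment effects".

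**The concern.** There are two separate problems in 2b.

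**Adjustment on one side only.** A regression coefficient is adjusted for baseline only if outcome and predictor are both cleared of baseline. Here only the outcome is. A predictor correlated with baseline severity then has part of its own effect removed in the first step, and part of the other predictors' effects may be moved onto it. The Introduction itself says that multiple loss, witnessing, and legal and financial consequences are thought to worsen distress, so some correlation with baseline is plausible.

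**No untreated comparator.** Everyone in these regressions is receiving CBT. At this stage condition separates immediate from delayed treatment, not treated from untreated. A slope shows who does better after CBT, which includes those who would have recovered anyway. If it is read as a treatment effect, a prognostic factor could be taken as a reason to tailor treatment.

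**Working it through.** **The plan's own figure.** The protocol gives no sample size for aim 2. Its only calculation is for hypothesis 1: "at least a medium effect size (f=0.25; based on prior research"), "with a power of 80" per cent, "an α of 0.017 (corrected for multiple testing, that is, 0.05/3"), and "a strong association (r=0.50) between the preassessment and postassessment". For the time × group interaction in a repeated-measures ANOVA with two occasions, λ = f²·N·2/(1 − r) = 0.0625 × 46 × 2/0.50 = 11.5 with 1 and 44 degrees of freedom. Power is 81.4%, and 46 is the smallest even total that reaches 80%. So 46 reproduces. It and the recruitment target of 55 are used below only as the available N.

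**Step 1: one predictor in 2b.** Let x and the pretreatment score be standardised with correlation r, and let post = β·pre + g·x + error.
- The slope of post on pre alone is β + g·r.
- The residual gain is therefore g·x − g·r·pre + error.
- Regressing this on x gives g − g·r·r = g(1 − r²).

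The protocol gives no r, so a range is assumed:

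| assumed r | 0 | 0.1 | 0.3 | 0.5 | 0.6 |
|---|---|---|---|---|---|
| two-step ÷ one-step coefficient | 1.00 | 0.99 | 0.91 | 0.75 | 0.64 |

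A simulation with one million records gave the same ratios.

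**Step 2: two predictors in 2b.** With uncorrelated x₁ and x₂, the same algebra gives b₁ = g₁ − r₁(g₁r₁ + g₂r₂). With assumed values:

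| r₁, r₂ | true g₁, g₂ | arithmetic | b₁ |
|---|---|---|---|
| 0.4, 0.4 | 0.10, 0.50 | 0.10 − 0.4(0.04 + 0.20) | 0.004 |
| 0.4, −0.4 | 0.10, 0.50 | 0.10 − 0.4(0.04 − 0.20) | 0.16 |
| 0.4, 0.4 | 0, 0.50 | 0 − 0.4(0.20) | −0.08 |
| 0.4, 0.4 | −0.20, 0.40 | −0.20 − 0.4(−0.08 + 0.16) | −0.23 |

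So a coefficient can nearly vanish, grow, or appear where the truth is zero. Simulation agrees with all four rows to within 0.002.

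**Step 3: treated phases only.** If x has a prognostic effect p without treatment and changes the treatment effect by m, the slope among treated people is p + m.
- p = 0.30, m = 0: slope 0.30.
- p = 0, m = 0.30: slope 0.30.
- p = 0.30, m = −0.30: slope 0.00.

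The first two cases cannot be told apart, and in the third a real moderator is invisible. The one-step model does not cure this, because it is a matter of which data are used.

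**Step 4: aim 2a.** Here both sides are residualised, each on its own pretreatment score, so step 1 does not carry over. With one correlate and a true coefficient of 0.4 (before standardising), simulated two-step ÷ one-step ratios ran from 0.71 to 1.13 over assumed patterns of cross-lagged effects, and were 1.00 without cross-lags.

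**Step 5: what the randomised phase could add.** Consider a predictor × condition term with a binary predictor split 50/50, adjusted for a baseline correlated 0.50 with outcome. Its standard error is √0.75 × √(16/N), in SD units of the outcome: 0.51 at N = 46 and 0.47 at N = 55. Power at two-sided 0.05 (normal approximation):

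| assumed interaction (SD) | 0.5 | 0.8 | 1.0 |
|---|---|---|---|
| N = 46 | 16% | 35% | 50% |
| N = 55 | 19% | 40% | 57% |

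**The case against.** - **The protocol already discloses the limit.** It says that moderators cannot be formally tested, calls aim 2 exploratory, and in the Discussion only expects to improve knowledge. This stands against any reading that it promises a moderator test, or that prognostic factors will certainly be reported as tailoring factors. It does not remove the inconsistency: the objectives still speak of impact on treatment effects and the Discussion of whom CBT works best for, and an exploratory analysis still needs a target it can estimate.
- **The bias may be small.** No correlation with baseline is given, and entry is restricted to people above symptom thresholds, which may weaken it. At r = 0.1 the one-predictor loss is 1%. This stands.
- **A reader might infer that two-step scores always shrink coefficients, so that tests are merely conservative and true predictors are missed.** That holds for a single predictor. The protocol plans multiple regression, and step 2 shows bias in either direction.
- **A reader might extend both criticisms to 2a.** The text does not support this. Aim 2a concerns change within online CBT, which treated phases fit, and the direction of any two-step bias there is not fixed.
- **Residual gain scores follow cited earlier research.** Precedent explains the choice but does not supply the missing adjustment in 2b.

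**Conclusion.** The point holds for aim 2b. The planned regression adjusts the outcome but not the predictors for baseline, so its coefficients are biased whenever predictors correlate with the pretreatment score. With one predictor the factor runs from 1.00 to 0.75 for assumed r between 0 and 0.5; with several, size and direction depend on correlations that the protocol does not give. Independently of any assumed r, treated-only data with condition as a main effect identify predictors of outcome under treatment, not differential benefit. The wording in Study objectives and the Discussion therefore goes beyond both the analysis and the stated limitation.

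This is a correction to an exploratory secondary aim that should be made. It does not touch hypothesis 1, and for 2a it supports at most a sensitivity check.

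**What to change.** - **Aim 2b model.** Regress the post-treatment (or follow-up) score on the pretreatment score, condition and the predictors in one model. Cost: one extra term, no new data.
- **Aim 2b wording.** Describe the results as exploratory predictors of outcome among treated participants. Bring the treatment-effect wording in Study objectives and the for-whom sentence in the Discussion into line with the limitation on moderators. Cost: a narrower conclusion.
- **Optional.** Explore predictor × condition terms in the randomised comparison already scheduled (T1 to the 12- and 20-week assessments, before the waitlist arm starts treatment). Label these exploratory and report intervals, since power is low at 46 to 55 people.
- **Aim 2a.** Keep the treated-phase data. At most add the outcome's pretreatment score or a one-step sensitivity analysis. A full one-step model is not simpler: with five correlates it has 5 pre-scores + 5 post-scores + outcome baseline + condition = 12 terms, against 5 + 1 = 6 now.

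The protocol states that recruitment had not begun at submission, so on that footing the change could be made before any outcome data were seen.
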